#### Termination criteria

2.2.4

1)Incomplete or imperfect data.2)Unwillingness to cooperate with or failure to complete the clinical study.

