**Fig. 1 fig1:**
[figure not shown]
The flow chart of the trial.

This is a randomized controlled multicenter clinical trial comprising two parallel groups. From January 2024 to June 2025, 140 patients meeting the diagnostic criteria and syndrome types of UC will be recruited. During the recruitment process, potential participants meeting the inclusion criteria will be thoroughly informed about the study's purpose, examinations, intervention measures, and follow-up procedures. Upon obtaining informed consent, eligible subjects will be randomly assigned to two groups in a 1:1 ratio. The groups will receive either JPQC combined with mesalazine or mesalazine intervention for 12 weeks. The UC patients will be followed up again after 6 months. The schedule details are listed in Table 1.

**Table 1 tbl1:** Schedule of trial.

Period	enrollment	baseline	treatment			follow-up
time points	week-1	week 0	week 4	week 8	week 12	week 24
patients						
Informed consent	✓					
Inclusion/Exclusion criteria	✓					
Medical history	✓					
Physical examination	✓					✓
Laboratory examination	✓					✓
Randomization	✓					
Intervention						
Jianpi Qingchang decoction(JPQC) group	JPQC:two times daily; + mesalazine: 1g/three times daily					
Mesalazine control group	1g/three times daily					
Outcomes						
Inflammatory bowel disease fatigue scale(IBD-F)		✓	✓	✓	✓	✓
Inflammatory Bowel Disease Questionnaire (IBDQ)		✓	✓	✓	✓	✓
TCM symptom efficacy		✓	✓	✓	✓	✓
Modified Mayo score		✓			✓	✓
Simple clinical colitis activity index (SCCAI)		✓				
Intestinal microbial diversity and non-targeted metabonomics		✓			✓	
Trial evaluation						
Safety of medicine		✓	✓	✓	✓	✓
Adverse event		✓	✓	✓	✓	✓
Reasons of drop-outs or withdrawals		✓	✓	✓	✓	
Patient's compliance					✓	

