#### Withdrawal criteria

2.2.5

1)Poor compliance with medication, not adhering to the required medication schedule.2)Loss of follow-up, patients who do not cooperate with reexamination and return visit3)Self-withdrawal from clinical observation for personal reasons.4)Occurrence of allergies or serious adverse reactions during taking medicine.

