### Statistical analysis

2.7

Statistical analysis will be conducted using SPSS 24.0 software. Descriptive statistics for measurement data will include mean ± standard deviation ($\bar{X}$ ± S) for data conforming to normal distribution. Two independent samples t-tests will be employed for comparing means, and variance analysis for multi-sample comparisons. Nonparametric tests will be used for data not conforming to normal distribution. Counting data will be analyzed using the χ^2^ test, and rank sum test for rank data. Correlation analysis between two variables will use linear correlation for bivariate normal distribution data and Spearman rank correlation for non-bivariate normal distribution or graded data. A significance level of *P* < 0.05 will be considered statistically significant. The study will also provide statistical descriptions of adverse events, adverse reactions, dropout rates, and rejections during treatment.

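### Sections 2.2.4 and 2.2.5 let randomised patients be removed for imperfect data or poor compliance without keeping them in follow-up, so the comparison risks becoming one of compliant completers

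*Protocol article*

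**What the plan says.** Section 2.2.4 (Termination criteria) has two entries: "Incomplete or imperfect data" and "Unwillingness to cooperate with or failure to complete the clinical study".

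Section 2.2.5 (Withdrawal criteria) has four. The first is "Poor compliance with medication, not adhering to the required medication schedule". The second is loss to follow-up, described as "patients who do not cooperate with reexamination and return visit". The third is the patient's own decision to leave. The fourth is "Occurrence of allergies or serious adverse reactions during taking medicine".

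Section 2.7 (Statistical analysis) promises "statistical descriptions of adverse events, adverse reactions, dropout rates, and rejections during treatment". Table 1 has a row for "Reasons of drop-outs or withdrawals", ticked from baseline to week 12. It schedules IBD-F and adverse events at every visit from baseline to week 24, and records compliance once, at week 12.

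Under section 2.3 the experimental arm takes the decoction twice daily on top of mesalazine three times daily, with timing rules for both. The control arm takes mesalazine alone. Section 2.2.6 raises 56 patients per arm to 70 to allow for 20% dropout.

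**The concern.** Incomplete data and poor compliance become known only after allocation, and both can depend on how the patient is doing and on how burdensome the assigned treatment is. A patient in the experimental arm has two products to adhere to; a control patient has one. With no placebo or blinding described, staff who judge whether a record is imperfect may know which arm it belongs to. The outcome is fatigue, which the Discussion itself calls subjective.

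The article does not separate stopping medication from leaving the study. If the criteria are followed as written, a patient removed at week 4 for poor compliance may have no IBD-F score at weeks 8, 12 or 24. An all-randomised analysis named later in another document could not recover scores that were never collected. What would be at stake is the comparability of the arms: a contrast of patients who took their treatment and have clean records estimates something other than the effect of assignment, and may flatter or penalise JPQC depending on who was removed.

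**Working it through.** **1. The plan's own figure.** Section 2.2.6 starts from 56 per arm and 20% dropout: 56 / (1 - 0.20) = 70 per arm, 140 in total. This reproduces. It means a planned loss of 0.20 x 70 = 14 patients per arm, with 56 per arm expected to remain.

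**2. Which criteria matter.**
- Loss to follow-up and self-withdrawal: ordinary events that wording cannot prevent.
- Withdrawal for allergy or a serious reaction: an ordinary safety provision, which need not end data collection.
- Incomplete or imperfect data: a judgement about records, with no evident role in deciding treatment and no threshold.
- Poor compliance: a reason to record non-adherence, not in itself a reason to stop measuring the outcome. Table 1 as printed records compliance only at week 12, so a withdrawal based on that entry would come when the treatment period is already over.

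The last two are the ones that are badly fixed.

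**3. Illustration on the score scale.** From the document: 20% removed, 56 per arm left. Assumed: no true effect; those removed from the JPQC arm would have scored d = 0.5 to 1.0 SD worse than those kept; control losses are random; the comparison uses only those kept; SD of 1 in each arm; two-sided 5% test (section 2.7 gives P < 0.05 without a side).
- Bias = 0.20 x d = 0.20 x 0.5 = 0.10 SD, up to 0.20 x 1.0 = 0.20 SD, favouring JPQC.
- Standard error = sqrt(2/56) = 0.189 SD.
- Bias / SE = 0.10 / 0.189 = 0.53, up to 0.20 / 0.189 = 1.06.
- Rejection probability = 1 - Phi(1.96 - bias/SE) + Phi(-1.96 - bias/SE) = 0.083, up to 0.185.
- If control losses are equally selective, the two shifts cancel: bias 0 and type I error 5%.

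**4. Illustration on the effective-rate scale.** Assumed: a true rate of 71% in both arms (the control rate in section 2.2.6) and 30% among those removed. Rate among those kept = (0.71 - r x 0.30) / (1 - r), where r is the fraction removed.

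| Removed, JPQC v control | Rate among those kept | Spurious difference | Two-sided rejection |
|---|---|---|---|
| 20% v 20% | 81.2% v 81.2% | 0 | 5% |
| 25% v 15% | 84.7% v 78.2% | 6.4 points | about 14% |
| 30% v 10% | 88.6% v 75.6% | 13 points | about 45% |
| 10% v 30% | 75.6% v 88.6% | -13 points | about 45%, against JPQC |

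The size and the direction both depend on how removal differs between the arms, and the document gives no figure for that.

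**The case against.** The strongest objection is that nothing in the article excludes anyone from the analysis. A reader might infer a completers-only analysis from three things: the criteria themselves, the phrase "dropout rates, and rejections during treatment" in section 2.7, and the inflation from 56 to 70. None of them establishes it. The criteria do not mention analysis. Section 2.7 adds a description of dropouts and rejections, and the latter term is undefined. Allowing for dropout in the sample size is routine. The analysis set and the missing-data method are commonly left to the full protocol or the SAP, so their absence from an article is not a fault in itself. This objection stands, and it limits the point to a risk created by sections 2.2.4 and 2.2.5.

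A reader might also infer that safety data are lost. The documents do not support that: Table 1 schedules adverse events at every visit, section 2.7 commits to describing them, and a reaction that leads to withdrawal would be captured. What is unstated is follow-up after withdrawal.

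Nor does the article show that removal would fall mainly on the JPQC arm or would favour it. The added decoction makes unequal removal plausible, but both its direction and its size are assumed.

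The objection does not dispose of the two criteria. They are stated rules that act at the stage of data collection. An SAP can say who is analysed, but it cannot supply outcomes from patients whose participation was ended.

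**Conclusion.** The concern holds as a risk that arises from stated wording. Two criteria, imperfect data and poor compliance, allow randomised patients to be removed for reasons that arise after allocation, are partly discretionary and may be related to arm, with nothing to say that their outcomes are still collected. It would be too strong to say that the comparison is completers-only or that randomisation is broken.

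The 8% to 18% type I error is an illustration. Of its inputs, only the 20% loss and the 56 per arm come from the document. The 0.5 to 1.0 SD deficit, and its confinement to the JPQC arm, are assumptions. The range runs down to no bias at all when losses are alike in both arms. The change is worth making because it costs little and removes a source of bias that analysis cannot fully repair.

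**What to change.** - In section 2.2.4, delete incomplete or imperfect data as a termination criterion. Handle data quality by queries and by the missing-data method.
- In section 2.2.5, state that poor compliance or stopping study medication does not end collection of IBD-F and adverse events, which continue through weeks 12 and 24 unless consent is withdrawn. Record non-compliance as data.
- In section 2.7, state that the primary comparison includes all randomised patients in their allocated arm, with a named missing-data method, and that completers are a sensitivity analysis. If the full protocol or SAP already says this, a cross-reference is enough. The method has to be specified explicitly: section 2.7 currently lists t-tests, analysis of variance, nonparametric and chi-squared tests, and no longitudinal model that would deal with missing visits.

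The rules on when treatment is stopped are not touched by any of this.

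The cost is wording in three sections, the choice of a missing-data method, and modest extra effort to keep in contact with patients who stop their medication. The estimated effect may be somewhat smaller than among compliant completers.

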#### Withdrawal criteria

2.2.5

1)Poor compliance with medication, not adhering to the required medication schedule.2)Loss of follow-up, patients who do not cooperate with reexamination and return visit3)Self-withdrawal from clinical observation for personal reasons.4)Occurrence of allergies or serious adverse reactions during taking medicine.

#### Sample sizes

2.2.6

Based on the literature findigns, the control group treated with mesalazine showed a 12-week effective rate of 71 % [17], while the experimental group treated with JPQC recipe and mesalazine exhibited an effective rate of 94.12 % in 12 weeks [18]. Considering a clinical difference to improve the effective rate, with α set at a unilateral level of 0.05 and β at 0.10, the sample size calculation was performed using the formula$$n=\frac{{2\bar{p}\bar{q}\left(Z_{\alpha }+Z_{\beta }\right)}^{2}}{{\left(p1-p2\right)}^{2}}$$

This yielded a sample size of approximately 56 cases for each group (n1 = n2 ≈ 56 cases). Accounting for a dropout rate of 20 %, the study required a total of 140 cases, with 70 patients in the control group and 70 patients in the test group.

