#### Primary outcome

2.4.1

The primary outcome of the study is the inflammatory bowel disease fatigue scale(IBD-F), which will be measured at baseline and 4, 8, 12 weeks after randomization. The IBD-F consists of 3 parts. Possible scores are 0–20 and 0–120 in part I and II, respectively. If the ‘not applicable – N/A’ (not applicable) option is checked (questions 3, 4, 9, 12, 13, 14), a corrected result has to be calculated from the following formula: Corrected result = actual total result/(120 – number of N/As × 4) × 120 [19].

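### The sample size and its 90% power rest on an undefined effective rate, not on the primary IBD-F score, and the stated one-sided alpha does not give the stated 56 per arm

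*Protocol article*

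**What the plan says.** Section 2.2.6 (Sample sizes) takes two rates from two cited sources: "the control group treated with mesalazine showed a 12-week effective rate of 71 % [17]" and, for JPQC plus mesalazine, "exhibited an effective rate of 94.12 % in 12 weeks [18]". It gives the aim of the calculation as "Considering a clinical difference to improve the effective rate" and applies a two-proportion formula "with α set at a unilateral level of 0.05 and β at 0.10". The result is given as "This yielded a sample size of approximately 56 cases for each group", and then: "Accounting for a dropout rate of 20 %, the study required a total of 140 cases".

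Section 2.4.1 (Primary outcome) names a different quantity: "The primary outcome of the study is the inflammatory bowel disease fatigue scale(IBD-F)". That scale is described by its score ranges, 0 to 20 for Part I and 0 to 120 for Part II, and is measured at baseline and weeks 4, 8 and 12. No response cut-off is given. The abstract also names IBD-F as primary.

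Section 2.7 (Statistical analysis) says for measurement data: "Two independent samples t-tests will be employed for comparing means", with nonparametric tests where normality fails. It sets P < 0.05 without saying whether the test is one- or two-sided.

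**The concern.** A sample-size statement should say what the trial can detect on its primary outcome. This one concerns a binary variable that is never defined, while the primary outcome is a score. No IBD-F difference, SD or response rate appears anywhere in the article, so the β of 0.10 cannot be carried over to fatigue.

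The headline question is whether JPQC relieves fatigue. Without a planning difference on IBD-F, nobody can judge in advance whether 140 patients suit that question, or say afterwards what effect the trial was built to find.

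The same paragraph has a second defect: its stated alpha and its stated result do not agree. Anyone rewriting it needs to know which of the two the figure of 56 reflects.

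**Working it through.** **1. The plan's own figure**

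Inputs from section 2.2.6: p1 = 0.71, p2 = 0.9412, α = 0.05 (stated as one-sided), β = 0.10, 20% dropout.

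Formula in the article: n = 2·p̄·q̄·(Zα + Zβ)² / (p1 − p2)².

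- p̄ = (0.71 + 0.9412)/2 = 0.8256, and q̄ = 0.1744
- 2·p̄·q̄ = 0.28797
- (p1 − p2)² = 0.2312² = 0.053453

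| Alpha | Zα + Zβ | Squared | n per arm |
|---|---|---|---|
| one-sided 0.05 (as stated) | 1.645 + 1.282 = 2.926 | 8.564 | 0.28797 × 8.564 / 0.053453 = 46.1 |
| two-sided 0.05 | 1.960 + 1.282 = 3.242 | 10.507 | 0.28797 × 10.507 / 0.053453 = 56.6 |

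The stated 56 matches the two-sided line only. Other one-sided versions do not reach it either: 45 (Fleiss), 53 (with continuity correction), 42 (unpooled variance) and 41 (arcsine). The dropout step is sound: 56/0.8 = 70 per arm, 140 in total. On the stated one-sided inputs the result would have been 47 per arm, and 47/0.8 = 58.75, so 59 per arm and 118 in total.

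At 56 per arm, power for 71% against 94.12% is about 91% two-sided and 95% one-sided. Both figures concern the effective rate only.

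**2. What 56 per arm offers on a score**

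The article gives no IBD-F difference or SD, so the difference has to be expressed in SD units over an assumed range. Method: two-sample t-test, noncentral t, 56 evaluable per arm, 110 degrees of freedom, noncentrality d·√(56/2).

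| | two-sided 0.05 | one-sided 0.05 |
|---|---|---|
| Difference for 90% power | 0.62 SD | 0.56 SD |
| Difference for 80% power | 0.53 SD | 0.47 SD |
| Power at 0.5 SD | 75% | 84% |
| Power at 0.4 SD | 56% | 68% |
| Power at 0.3 SD | 35% | 47% |

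Hand check with the normal approximation: (1.960 + 1.282)·√(2/56) = 3.242 × 0.1890 = 0.61 SD for 90% power two-sided, which agrees with the table to within 0.01.

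**3. Whether the text links the two endpoints**

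The effective rate is used only in section 2.2.6. Section 2.4.1 gives score ranges and a correction for items marked not applicable, but no threshold. Section 2.4.2.2 (TCM symptom efficacy) is the listed outcome closest in name; it is secondary, and its main symptoms are bowel symptoms. No sentence says that the effective rate comes from either.

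**The case against.** **The effective rate may be a real trial variable.** It could derive from TCM symptom efficacy, whose criteria come from a cited table, and section 2.7 provides a χ² test for counts. A dichotomised IBD-F is not strictly excluded either. This stands as far as it goes, so the accurate statement is that the rate is undefined and not linked to the primary outcome, rather than that no such outcome could exist. It does not rescue the paragraph. In the first case the trial is sized on a secondary outcome; in the second, section 2.4.1 lacks the cut-off.

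**A separate analysis plan could supply the details.** It could add an SD. But the article does state a sample-size basis, and it is for another quantity, so this is a mismatch in the text rather than something left for later.

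**The sizing paragraph says one-sided.** This is fair, and it is why both columns are shown above. The two-sided column leads because only two-sided alpha yields 56.

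**Stronger readings that the article does not support.**

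- A reader might infer that the trial is underpowered for fatigue. Nothing shows that: about 0.6 SD or more would be well covered.
- A reader might infer that a null IBD-F result would be uninterpretable. A confidence interval for the group difference would still show which effects the data exclude.
- A reader might discount the gap between the two rates because it crosses two sources. The sources are not at hand, so their comparability cannot be judged and no weight is put on this.

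**Conclusion.** The point holds as a mismatch between the sizing and the primary outcome. The 90% power in section 2.2.6 belongs to an undefined binary variable, and the power of the IBD-F comparison is unstated and cannot be derived from the article. The alpha label and the result in that paragraph also contradict each other: 46.1 against 56.6 per arm.

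The practical size depends on the expected IBD-F effect, which is not given. At two-sided 0.05, 56 evaluable per arm is adequate from about 0.6 SD upwards, and power drops to 75%, 56% and 35% at 0.5, 0.4 and 0.3 SD. These figures assume a t-test on one IBD-F variable at one time point, equal SDs in the two arms and the planned 20% dropout. The paragraph should be corrected before the trial is described as having 90% power for its primary outcome.

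**What to change.** Keep 140 patients and rewrite section 2.2.6, with a matching line in section 2.4.1:

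1. Name the primary variable: IBD-F Part I or Part II, at week 12. The two parts have different ranges and the article does not say which one is primary, so a detectable difference has no meaning until this is chosen.
2. State alpha as two-sided 0.05, which is what 56 reflects, remove the one-sided label, and say two-sided in section 2.7 as well.
3. Replace the power statement with, for example: with 56 evaluable patients per arm and two-sided alpha of 0.05, the trial has 90% power for a between-group difference of 0.62 SD, and 80% power for 0.53 SD, in the named IBD-F part at week 12.
4. Convert these differences to IBD-F points with a justified, stated SD assumption and a range around it. Say whether a difference of that size is plausible and important to patients. The article reports no IBD-F SD, so its source has to be given.
5. Stop presenting the effective-rate calculation as the power for the primary outcome. If it is kept as background, define the rate and say which outcome it belongs to.

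The cost is one rewritten paragraph and two short conforming edits, with no extra patients. The downside is that the stated power becomes less favourable if the expected IBD-F effect is below about 0.6 SD.

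### The printed sample-size formula with the stated one-sided alpha of 0.05 gives 47 per group, not 56; the inputs and the result need reconciling, although 140 patients can stand

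*Protocol article*

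**What the plan says.** Section 2.2.6 (Sample sizes) of the protocol article gives every input. For control, "the control group treated with mesalazine showed a 12-week effective rate of 71" per cent is taken from the literature; the combination arm "exhibited an effective rate of 94.12 % in 12 weeks". The error rates are set "with α set at a unilateral level of 0.05 and β at 0.10". The section says "the sample size calculation was performed using the formula" n = 2·p̄·q̄·(Zα + Zβ)² / (p1 − p2)², which has no continuity correction. It then reports: "This yielded a sample size of approximately 56 cases for each group". The last step reads "Accounting for a dropout rate of 20 %, the study required a total of 140 cases", which is 70 per group. Allocation is equal (section 2.1: "eligible subjects will be randomly assigned to two groups in a 1:1 ratio").

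Section 2.7 (Statistical analysis) says only that P < 0.05 "will be considered statistically significant"; it does not say whether that is one-sided or two-sided.

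**The concern.** Section 2.2.6 gives both the inputs and the answer, so the calculation can be repeated, and the answer does not follow. The gap is too large for rounding: 56 is 9 patients per group, or 19% (9/47), above what the stated inputs require.

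The input most likely to be misstated is the sidedness of alpha, and the word unilateral in section 2.2.6 is the article's only statement on sidedness. A one-sided 0.05 test carries a 5% chance of wrongly claiming benefit for JPQC; a two-sided 0.05 test carries 2.5% in that direction. What is at stake is a clear statement of the error rate the trial was designed for, not a shortage of patients.

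**Working it through.** **Inputs** (section 2.2.6): p1 = 0.71, p2 = 0.9412, alpha = 0.05 one-sided, beta = 0.10, dropout 20%. Allocation is 1:1 (section 2.1).

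**Common terms**
- p̄ = (0.71 + 0.9412)/2 = 0.8256 and q̄ = 0.1744, so 2p̄q̄ = 0.2880
- (p1 − p2)² = 0.2312² = 0.05345
- Zβ = 1.282

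**Attempt to reproduce 56 from the stated inputs**
- Zα = 1.645; (1.645 + 1.282)² = 8.565
- n = 0.2880 × 8.565 / 0.05345 = 46.1, so 47 per group
- With dropout: 47/0.8 = 58.75, so 59 per group and 118 in total

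The printed 56 is not reproduced.

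**Same formula and beta, two-sided alpha 0.05**
- Zα = 1.960; (1.960 + 1.282)² = 10.507
- n = 0.2880 × 10.507 / 0.05345 = 56.6
- This gives 56 if truncated and 57 if rounded up

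**Solving backwards from n = 56 with beta 0.10**
- √(56 × 0.05345 / 0.2880) = 3.224
- 3.224 − 1.282 = 1.942, a one-sided alpha of about 0.026, close to two-sided 0.05

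**The dropout step**
- 56/0.8 = 70 per group, 140 in total. This step is correct.

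**Other routes to a figure near 56**
- 47 × 1.2 = 56.4: dropout added once here and again in 56/0.8
- One-sided 0.05 with a continuity correction added to the printed formula: 54.4, so 55
- One-sided 0.05 with beta 0.05 by the Fleiss formula: 56

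Each of these departs from something the section states.

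**Power at 56 evaluable per group, by the printed formula**
- One-sided 0.05: 3.224 − 1.645 = 1.579, power 94.3%
- Two-sided 0.05: 3.224 − 1.960 = 1.264, power 89.7%

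Using separate variances under the alternative instead, the figures are 95.1% and 90.8%.

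**The case against.** The strongest reply is that nothing is lost. The trial enrols more than the stated one-sided design needs and has about 90% power under a two-sided test, so no enrolment figure has to change. That stands, and it limits how serious the point is. The section also calls its figure approximate, so the difference between 56 and 57 is trivial; the difference between 47 and 56 is not.

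A reader might infer that 56 can only have come from a two-sided calculation, so that alpha is proven to be the wrong input. The article does not support that. Two-sided 0.05 is the nearest fit within the printed formula and stated beta, but 47 × 1.2 = 56.4 rounds to 56 directly, whereas 56.6 reaches 56 only by truncation. What is shown is that the four stated elements conflict, not which one is at fault.

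A reader might also infer that the sponsor plans to claim success at a two-sided p of up to 0.10. No section says so. Section 2.7 sets P < 0.05, names ordinary t, χ² and rank tests, and mentions no one-sided test. Its silence on sidedness is not an error in itself, since that detail may be in an analysis plan that is not shown. It needs a word only so that it agrees with a corrected section 2.2.6.

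**Conclusion.** The inconsistency is real. The stated inputs give 47 per group (59 after dropout, 118 in total), against a printed 56 (70 and 140), and no other section resolves it. The most plausible explanation is a two-sided alpha of 0.05 described as one-sided, but this is not proven.

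The direction is conservative. If the assumed rates of 71% and 94.12% hold and 56 per group are evaluable, power is 94.3% or 89.7% by the printed formula, depending on sidedness, so 140 patients can stand. These figures describe a comparison of effective rates. The primary outcome in section 2.4.1 is the IBD-F fatigue score, for which the article defines no effective rate, so they should not be read as power for the primary outcome. This should be fixed, but it does not threaten the trial.

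**What to change.** The sponsor should go back to the calculation, confirm which input produced 56, and make section 2.2.6 agree with it. If no record shows otherwise, the default is:

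- in section 2.2.6, replace the one-sided 0.05 with two-sided 0.05, keep 56 evaluable and 70 randomised per group, and give power as about 89.7% for the effective-rate comparison;
- in section 2.7, state that P < 0.05 is two-sided.

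The cost is two wording changes and a stated power 0.3 points below 90%, with no extra patients. Rounding up to 57 while keeping 140 would create a new error: 57/0.8 = 71.25, so 72 per group and 144 in total. If a one-sided 0.05 design was truly intended, the section should show 47 per group, 59 after dropout and 118 in total, or explain why 140 are enrolled, and section 2.7 should say that the test is one-sided.
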